### Outcomes

The primary outcome of the study is the feasibility of the developed intervention. We assess whether it is possible to recruit patients, to conducte the developed intervention with them, and measure the outcomes.

In addition, an estimate of the effect size in preparation of an RCT will be conducted, and the feasibility of the corresponding assessments investigated. For the later RCT the primary outcome is health-related quality of life (measured via Short-Form Health Survey-12; SF-12). Secondary outcomes are somatic symptoms (Patient Health Questionnaire-15; PHQ-15 and Long/Post-COVID symptoms), depressive symptoms (PHQ-9), anxiety (Generalized Anxiety Disorder-7; GAD-7), fatigue (Fatigue Assessment Scale; FAS), perceived stress (Perceived Stress Questionnaire-20; PSQ-20), work ability (Work Ability Score; WAS), mental well-being (WHO-Five Well-Being Index; WHO-5), illness perception (Revised Illness Perception Questionnaire; IPQ-R), symptom-related thoughts, feelings and behaviour (Somatic Symptom Disorder - B Criteria Scale; SSD-12) and work stress (Psychosocial Safety Climate-4; PSC-4). The questionnaires are used in both groups at baseline (t1), directly post-intervention (t2) and six months after baseline assessment (t3). The analysis of intervention effects compared to control group is only conducted at the end of the intervention in the primary intervention group (comparison of intra-individual improvement). Later measurements are only used to assess if the effects in the early and late (after waiting) intervention group are similar or whether the effects are maintained after the intervention phase. Additionally, adverse childhood experiences (Childhood Trauma Screener; CTS) are assessed at t1 and treatment satisfaction (ZUF-8) at t2.

Ecological momentary assessments (EMAs) will be conducted weekly using a newly developed questionnaire consisting of a set of five items. EMAs are used to track participants’ current condition (quality of life, physical/psychological well-being, concentration, everyday abilities).

As an additional part of the study, blood samples are taken at t1 and t2 to analyse changes in the IL-1Beta, IL6, TNF cytokine triad which has been associated with Long/Post-COVID-sequelae in a recent study (29).

Blood sampling is performed only for those participants who have additionally given their consent for this part of the study.

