### Plans for collection, laboratory evaluation and storage of biological specimens for genetic or molecular analysis in this trial/future use

Plasma will be separated from whole blood by centrifugation at 1400 x g for 10 min. Remaining cell debris will be removed by high-speed centrifugation at 12000 x g for 10 min. Plasma samples will be stored at -80°C. Plasma cytokine levels will be quantified using bead-based multiplex flow cytometry kits from Biolegend (LEGENDplex Human B cell Panel (13-plex), Human Anti-Virus Response Panel (13-plex)). Measurements will be performed on a BD FACSCelesta flow cytometer (compare (29) for more methodological details).

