## Statistical methods

### Statistical methods for primary and secondary outcomes

The statistical analysis will be conducted utilizing descriptive analysis of primary and secondary outcomes (e.g. differences in mean and median). In an exploratory fashion, mixed-effect linear regression analysis adjusted for study site (random effect) will be used to check for differences between intervention and control groups regarding intraindividual differences in the primary outcome Health-Related Quality of Life (measured by SF-12) between enrolment (t1) and post-intervention assessment (t2). Covariates will be adjusted for if misbalance in characteristics at baseline assessment is more than 20%. In the same way, secondary outcomes will be analysed. These analyses will be also conducted to assess stability of changes i.e. comparing outcomes at t2 and t3. EMAs will be analysed using analysis of variance respectively trajectories approach to detect changes over time. Immunological parameters (i.e. cytokine levels) will be analysed in the same way as primary outcome – in case of non-normal distributions, transformation will be applied.

Additional analyses will be conducted regarding feasibility of recruitment, drop-out rate, therapist adherence and participant adherence.

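### Cytokine scale is left to a look at the data: fix the log scale in advance for all three cytokines and adjust for baseline instead of using a change score

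*Protocol article*

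**What the plan says.** In the protocol article, the section on statistical methods for primary and secondary outcomes states that "Immunological parameters (i.e. cytokine levels) will be analysed in the same way as primary outcome", and continues: "in case of non-normal distributions, transformation will be applied". The primary-outcome analysis it points to is a linear mixed model with site as random effect, introduced as exploratory, that looks for "differences between intervention and control groups regarding intraindividual differences in the primary outcome" between t1 and t2. Covariates enter only if they are imbalanced at baseline by more than 20%, so the baseline value is not adjusted for routinely.

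The Outcomes section sets the target: "blood samples are taken at t1 and t2 to analyse changes in the IL-1Beta, IL6, TNF cytokine triad". The section on additional consent provisions makes the blood module optional, with separate consent. The Sample size section gives 60 per arm on grounds of feasibility.

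**The concern.** The sentence does not determine the analysis.

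- **The trigger depends on the data.** Each cytokine is transformed or not once its distribution has been seen. No criterion and no transformation is named.
- **The object of the trigger is open.** It could be the t1 and t2 levels or their difference. The choice changes the quantity estimated. A log of the levels before differencing gives a ratio, while an untransformed difference gives an absolute change. A 30% fall is an absolute change of 0.30 × baseline, so on the absolute scale a patient with ten times the baseline contributes ten times the change.
- **The change score is not the efficient choice.** In a randomised comparison, change and baseline-adjusted analyses address the same arm effect, but adjustment has the smaller variance whenever the correlation is below 1.

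At stake is whether the results for the three cytokines, which the article treats as one triad, can be read side by side and taken into planning of the later RCT on one scale. The Discussion also hopes that cytokines will point to phenotypes with differential response, which needs a common and stable scale.

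**Working it through.** **The plan's own figure.** There is none to reproduce. The article states no effect size, SD or power for cytokines.

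**Inputs.** From the article: t1 and t2 samples, two arms, at most 60 per arm. Assumed, because the article gives no values: log-normal levels, SD of the log σ = 0.7 or 1.0, t1–t2 correlation ρ = 0.5 or 0.7, a true 30% fall in one arm (δ = |ln 0.70| = 0.357), 30 per arm as a case of partial uptake, and a two-sided 5% test. The site effect is left out.

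**Step 1: change score against baseline adjustment, both on the log scale.**

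- Variance of a log difference: 2σ²(1 − ρ).
- Residual variance of log t2 given log t1: σ²(1 − ρ²).
- Ratio of the second to the first: (1 + ρ)/2, which is 0.75 at ρ = 0.5 and 0.85 at ρ = 0.7.
- SE of the arm effect: √(2 × variance / n). Power comes from the noncentral t with noncentrality δ/SE and 2n − 2 or 2n − 3 degrees of freedom.

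Example with n = 30, σ = 0.7, ρ = 0.5:

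- Log difference: variance 2 × 0.49 × 0.5 = 0.49, SE √(0.98/30) = 0.181, noncentrality 1.97, power 0.49.
- Adjusted: variance 0.49 × 0.75 = 0.3675, SE √(0.735/30) = 0.157, noncentrality 2.28, power 0.61.

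| n per arm | σ | ρ | SE, log difference | Power | SE, adjusted | Power | Gain (points) |
|---|---|---|---|---|---|---|---|
| 30 | 0.7 | 0.5 | 0.181 | 0.492 | 0.157 | 0.610 | 11.8 |
| 30 | 0.7 | 0.7 | 0.140 | 0.707 | 0.129 | 0.775 | 6.8 |
| 30 | 1.0 | 0.5 | 0.258 | 0.274 | 0.224 | 0.348 | 7.4 |
| 30 | 1.0 | 0.7 | 0.200 | 0.418 | 0.184 | 0.477 | 5.9 |
| 60 | 0.7 | 0.5 | 0.128 | 0.790 | 0.111 | 0.892 | 10.2 |
| 60 | 0.7 | 0.7 | 0.099 | 0.947 | 0.091 | 0.972 | 2.5 |
| 60 | 1.0 | 0.5 | 0.183 | 0.491 | 0.158 | 0.609 | 11.8 |
| 60 | 1.0 | 0.7 | 0.141 | 0.706 | 0.130 | 0.774 | 6.8 |

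Simulation of the same settings agrees: 0.27–0.71 rises to 0.34–0.79 with 30 per arm, and 0.50–0.94 to 0.61–0.97 with 60.

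**Step 2: what untransformed differences would cost.** In simulation, power on raw differences is 0.15–0.46 with 30 per arm (log differences 0.27–0.71) and 0.25–0.75 with 60 (log differences 0.49–0.94). With no values below a detection limit, the raw-difference estimate is unbiased (0.99–1.00 of the true value), so the loss is one of precision.

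**Step 3: how often the trigger would fire.** The article names no criterion. Take a Shapiro-Wilk test at 5% as an assumption. It flags t1 levels in 99.5–100% of simulated trials, and arm-centred raw differences in 83–99% with 30 per arm and 98–100% with 60. If a log difference is used whenever it fires, power is close to that of log differences throughout. The Step 2 loss therefore applies only to the few cases where the trigger stays silent, or to a looser check such as visual inspection.

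**The case against.** The strongest reply is that the plan already provides for skewed data. The subject of the sentence is cytokine levels, so logging the t1 and t2 levels and then taking differences satisfies its wording. Under a formal test the trigger would nearly always fire. The analysis is introduced as exploratory ("In an exploratory fashion, mixed-effect linear regression analysis"), the module is optional, and no power is claimed for it. An analysis plan that is not shown may settle the scale.

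Most of this stands, and it rules out three stronger readings.

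- **That the plan takes logs of negative numbers.** About half of all differences are negative under no change, and 66–72% at a ratio of 0.70 with correlation 0.6, so a plain log of differences would indeed fail. But the article neither mentions a log nor says that differences are what is transformed. This is an ambiguity, not a demonstrated error.
- **That the raw-versus-log power gap is the cost of the written rule.** Step 3 shows that it is not.
- **That values below the assay's detection limit pull the result towards no change.** The article names the assay ("Plasma cytokine levels will be quantified using bead-based multiplex flow cytometry kits from Biolegend") but gives no limit, no share of values below it and no substitution rule. The direction depends on that rule. With 20% of values below the limit, half the limit as substitute gives 0.97–1.05 of the true log-scale effect, while one tenth of the limit gives 1.48–1.81. Such handling is also commonly left to a fuller document.

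What the reply does not answer is that the scale is still decided analyte by analyte after the data are seen, and that a change score is kept where baseline adjustment would be more precise.

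**Conclusion.** The point holds as a low-severity matter of analysis choice. The written rule leaves the cytokine scale open until the data are in, and it allows the three analytes to be reported on scales that cannot be compared. Fixing the log scale and adjusting for baseline gives one ratio scale and, under the stated assumptions, about 3–12 percentage points more power than log differences. The variance is 15–25% smaller at correlations of 0.7 and 0.5. These figures rest on log-normal levels and on assumed SD, correlation, effect and uptake, none of which the article gives. No bias in the planned estimate has been shown.

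**What to change.** Delete the condition on non-normality. State instead that for IL-1beta, IL-6 and TNF alike the t1 and t2 concentrations are log-transformed whatever their observed distribution. Log t2 is then modelled on arm, adjusted for log t1, with site as random effect, and the arm effect is reported as a ratio of geometric means with its confidence interval. If an analysis plan already fixes this, it is enough to bring the two texts into line.

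The cost is one or two sentences, settled before the cytokine data are examined. No new samples or measurements are needed. The small downside is that results appear as ratios and not as changes in pg/ml; descriptive medians by arm and time point can sit beside them for readers who want the original units.

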### Methods for additional analyses (e.g subgroup analyses)

In exploratory fashion, subgroup analyses comparing males and females and younger and older participants, dichotomized at median, will be conducted for the planning of subgroup analysis in the later RCT.

### Methods in analysis to handle protocol non-adherence and any statistical methods to handle missing data

Both, intention-to-treat and per-protocol analysis will be conducted to assess the extent of protocol violation. Single items missing within the outcome instruments, respectively, will be imputed by median, if less than 20% of items are missing.

Therapies are planned to be held over the course of 12 weeks. In case of any cancelled appointments therapies can be prolonged for up to two weeks. Participants who drop out before session four of the intervention will be replaced. Four missed sessions will be treated as non-adherence.

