### Sample size

A total of N = 120 participants will be assigned to the study arms, 60 to the waitlist with regular care arm and 60 to the PsyLoCo intervention arm. Case numbers are based on feasibility within a pilot trial.

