### Concealment mechanism

The allocation sequence will be stored in a CSV-file in a folder that is only accessible by the biometrician who creates the allocation sequence. It is uploaded to the randomization tool in RedCap. Only the responsible biometrician has access to the file. Once the project starts, the allocation sequence cannot be changed or accessed by anyone.

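### Replacing early drop-outs acts on one arm only, conflicts with the intention-to-treat analysis and, if the replaced are not counted, understates drop-out

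*Protocol article*

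**What the plan says.** The rule stands in the section on protocol non-adherence and missing data: "Participants who drop out before session four of the intervention will be replaced". The same section promises two analysis sets and gives their purpose: "Both, intention-to-treat and per-protocol analysis will be conducted to assess the extent of protocol violation". It also defines non-adherence: "Four missed sessions will be treated as non-adherence".

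Other sections bear on it:

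- **Outcomes**: feasibility is the primary outcome. The comparison with controls is made only when the first-treated group finishes therapy. An effect size is to be estimated for the later RCT.
- **Statistical methods for primary and secondary outcomes**: "Additional analyses will be conducted regarding feasibility of recruitment, drop-out rate, therapist adherence and participant adherence".
- **Sample size**: "A total of N = 120 participants will be assigned to the study arms", split 60 and 60. On the basis for this number: "Case numbers are based on feasibility within a pilot trial".
- **Sequence generation** and **Concealment mechanism**: allocation is stratified by centre in blocks of 4 and 6, and "Once the project starts, the allocation sequence cannot be changed or accessed by anyone". Neither section mentions replacements.
- **Plans to promote participant retention and complete follow-up**: once someone ends study participation, outcome collection stops.

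**The concern.** Intention-to-treat means that a participant counts in the allocated arm whatever happens after randomisation. A rule that substitutes another person because of a post-randomisation event works against that. Here the event, leaving before the fourth session, cannot occur on the wait-list before t2, and no matching rule is given for wait-list drop-outs. One arm is filtered for early persistence and the other is not.

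Two results are at stake. The first is feasibility: people who give up in the first three weeks are exactly those a pilot of a new 12-session manual needs to count. The second is the effect size carried into RCT planning, if early leavers are left out of the t2 comparison.

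**Working it through.** **1. The plan's own figures.** 60 + 60 = 120, and five treating sites with 24 each give 5 × 24 = 120. Both agree with the stated N. The number rests on feasibility, so there is no power calculation to reproduce, and no drop-out allowance is given.

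**2. Which arm the rule can reach.** The comparison uses change from t1 to t2. Wait-list participants start sessions only afterwards. The rule may apply to them later, but that lies outside the randomised comparison.

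**3. Adherence.** Someone who leaves before session four has attended at most 3 of 12 sessions and so missed at least 12 − 3 = 9. If sessions not attended after leaving count as missed, every early leaver meets the plan's own definition of non-adherence (four missed). Taking them out of both analysis sets would therefore hide part of the protocol violation that contrasting the two sets is meant to show.

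**4. Drop-out rate.** Let e be the probability of leaving before session four, and l the probability of leaving later among those who reach it. Both are assumptions (e = 5–20%, l = 10%), and replacements are assumed to leave at the same rates.

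- Intervention entrants needed to keep 60 past the cut: 60/(1 − e)
- Drop-out with everyone counted: e + (1 − e) × l
- Drop-out if replaced people are not counted: l

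| e | Entrants for 60 | Replaced | Drop-out, all counted | Drop-out, replaced not counted |
|---|---|---|---|---|
| 5% | 63.2 (64) | 3.2 | 14.5% | 10% |
| 10% | 66.7 (67) | 6.7 | 19.0% | 10% |
| 15% | 70.6 (71) | 10.6 | 23.5% | 10% |
| 20% | 75.0 (75) | 15.0 | 28.0% | 10% |

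The understatement is e × (1 − l), which is 4.5 to 18 percentage points. The reported figure stays at 10% whatever the early loss, so it carries no information about it.

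**5. Allocation.** A replacement put straight into the vacated slot is not randomised. One who takes the next entry in the 1:1 sequence has about an even chance of becoming a control. If enrolment stops at 120 randomised, the intervention arm keeps about 60 × (1 − e) past session four: 57, 54, 51 or 48 for the four values of e. If it continues until 60 are kept, about twice the entrants in the table are needed, for example 2 × 75 = 150 at e = 20%. Exactly 60:60 randomised and 60 retained in the intervention arm cannot both be guaranteed.

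**6. Effect estimate.** If early leavers would have changed by g SD less than those who stay, leaving them out shifts the intervention mean by e × g. With g assumed at 0.25–0.8 SD, this is 0.01–0.04 SD at e = 5% and 0.05–0.16 SD at e = 20%. The standard error of the difference at 60 per arm is √(2/60) = 0.18 SD. The number of replacements does not enter the formula: the shift comes from having no t2 values for early leavers, whether or not anyone takes their place.

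**The case against.** The strongest defence is that replacing someone need not mean deleting them. The section does not say that early leavers exit the intention-to-treat set or the drop-out denominator, and the plan commits to analysing both drop-out and adherence. Enrolling extra people while still counting everyone randomised would fit every sentence, and set membership is often left to a SAP. This stands in part: the understated rate in step 4 is conditional on the ordinary reading. But the article fixes an explicit rule, pairs it with an intention-to-treat promise, and gives no denominator that includes the replaced.

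A reader might infer that the rule itself inflates the effect by the amounts in step 6. The documents do not support that. They give neither a drop-out rate nor an outcome difference, and people may also leave because they have improved. The shift would remain if the rule were deleted, because the retention section also ends outcome collection for those who leave the study.

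A reader might also see a contradiction with the close of recruitment in mid-June 2023 (Trial status). There is none: recruitment opened in mid-March, so many participants could reach or miss session four while it was running.

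Finally, the 60:60 split and 24 per site are targets that further randomisation could modestly exceed, and the locked sequence does not forbid using further entries. That is fair, but the article does not say this is what happens.

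**Conclusion.** The rule is wrong as written. Within the randomised comparison it selects on a post-randomisation event in the intervention arm alone, and in its ordinary sense it conflicts with the intention-to-treat analysis stated beside it. If replaced people are not counted, intervention-arm drop-out of 14.5–28% would be reported as 10%, given assumed early loss of 5–20% and later loss of 10%. Neither rate comes from the document. The consequence for the effect estimate is unquantified and its direction unknown. The efficacy comparison is exploratory, so the main harm is to the feasibility result, with a secondary risk to the effect size used for the RCT.

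**What to change.** 1. Drop replacement in the analysis sense. State that every randomised participant stays in the allocated arm, in the intention-to-treat set and in the denominators for drop-out and adherence.
2. Report the number leaving before session four and the true number randomised, by arm.
3. Count any extra participants as additional, never in place of a leaver, and state that they enter only through the normal centre-stratified sequence. If replacements have already been enrolled, report how each was allocated.
4. Amend the retention section to separate stopping therapy from withdrawing consent, so that people who stop therapy without withdrawing are still asked for the t2 and t3 questionnaires. Without this, item 1 leaves early leavers in the set but without outcomes.

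Items 1 and 2 remain fully usable after recruitment has closed. The cost is a less favourable drop-out figure, fewer completers than the target of 120, and a small amendment to the retention section with the follow-up contacts it entails.

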### Plans to give access to the full protocol, participant level-data and statistical code

Given the pilot study approach, there is no plan to give access to the full protocol, participant level-data and statistical code.

## Oversight and monitoring

### Composition of the coordinating centre and trial steering committee

The study is coordinated at the institutions in Munich (TU), Magdeburg and Halle (Saale). Statistical and biomedical analyses are conducted at the Institute for Medical Epidemiology, Biometrics and Informatics at the university of Halle (Saale). Psychotherapeutic interventions are conducted at the psychosomatic departments of the university hospitals in Munich (TU), Magdeburg, Tuebingen, Ulm and Freiburg. At each study site an equal number of participants will be included (n=24). The coordinating staff meets regularly every two weeks. Full staff meetings are held monthly. Therapeutic sessions will be supervised in small groups of up to five therapists once a month by an experienced and senior specialist.

### Adverse event reporting and harms

Any adverse events will be documented. They will be discussed within the PsyLoCo consortium and reported to the ethical committees.

### Frequency and plans for auditing trial conduct

Annual project reports will be sent to the funding agency as requested.

